## SPECIFIC AIMS:

It is well-known that smokers suffer more complications and higher risk of mortality after surgery than non-smokers[^1^](#_ENREF_1)^,^[^2^](#_ENREF_2). Despite this knowledge, it is unclear what clinicians can do to minimize this risk. Surgery represents a 'teachable moment' that might encourage smokers to engage in permanent cessation[^3^](#_ENREF_3). Several small trials have shown that smoking cessation interventions can increase smoking cessation and reduce postoperative complications, particularly wound-healing complications, which can have an absolute risk reduction of up to 25%[^4-7^](#_ENREF_4). Smoking cessation initiated in the perioperative period can also promote long-term smoking cessation[^7-9^](#_ENREF_7). Despite the benefits of comprehensive smoking cessation interventions including nicotine replacement therapy, current standard of care at the SFVAMC does not routinely include specific preoperative smoking cessation pharmacotherapy or counselling. Although there is an urgent need for more data, e-cigarettes have been proposed as an alternative to nicotine replacement therapy that are at least as effective for smoking cessation[^10^](#_ENREF_10), and may be more acceptable to some patients[^11^](#_ENREF_11).

The main hypothesis of this pilot study is that the use of e-cigarettes and telephone counselling, compared to telephone counselling and transdermal nicotine replacement, in the perioperative period results in increased smoking cessation on the day of surgery and at 8-weeks after randomization in smokers presenting for elective surgery. As secondary hypotheses, the study will also assess the acceptability of e-cigarettes versus nicotine patches, postoperative complications within the first 30-days, length-of-stay in the PACU and hospital length-of-stay. We will examine the above hypotheses through the following aims:

**» Aim 1) To determine how e-cigarettes plus counselling compare to transdermal nicotine replacement plus counselling for the achievement of smoking cessation, when introduced prior to elective surgery in veterans.**

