We plan to carry-out a pilot randomized controlled trial with parallel design comparing e-cigarettes and telephone counselling with transdermal nicotine replacement and telephone counselling. Our primary outcome is smoking cessation on the day of surgery, as confirmed biochemically by exhaled carbon monoxide. Smoking reduction (self-reported cigarettes per day) of 50% or more and bedside spirometry readings will be assessed as secondary outcomes.

**» Aim 2) To determine the acceptability of e-cigarettes amongst veterans as an aid for smoking cessation and to determine the feasibility of recruitment, randomization, and follow-up procedures in preparation for large-scale trial.**

Through implementation of this pilot trial, we will determine the feasibility and acceptability of e-cigarettes for smoking cessation perioperatively in the veteran population and obtain the preliminary data necessary to run a larger trial on the effectiveness of e-cigarettes as a perioperative smoking cessation aid.

**» Aim 3) To determine the safety of e-cigarettes as a harm reduction strategy to achieve short-term perioperative smoking cessation.**

We plan to improve the overall knowledge of the safety of short-term e-cigarettes use through careful surveillance for adverse events and side effects.

**» Aim 4) To determine if e-cigarette use preoperatively is associated with a lower risk of complications postoperatively.**

We plan to measure the following secondary outcomes: postoperative complications and mortality within the first 30 days, post-anesthesia care unit (PACU) length-of-stay, and hospital length-of-stay. This will help us understand if e-cigarettes have the potential to be used for harm-reduction perioperatively.

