## Detailed Experimental Design and Methods:

**Study Design:** Randomized controlled trial with 2 parallel arms:

1) Electronic nicotine delivery device group (ENDD) + referral to the California Smokers' Helpline

2) Control group (referral to the California Smokers' Helpline plus transdermal nicotine replacement)

**Study population:** Adults presenting for elective surgery at the SFVAMC.

**Identification of subjects:** Potential subjects will be identified on the basis of operating room bookings and current smoking history at their preadmission evaluation in the Anesthesia Preoperative Clinic (APO clinic). We will aim to recruit patients at least 1 week preoperatively, but accept patients up to 3 days preoperatively so as to maximize the number of available subjects, but allow enough time to begin smoking cessation preoperatively. They will be seen for further evaluation of inclusion and exclusion criteria at the time of their usual preoperative assessment in the APO clinic, which according to a recent quality improvement audit, was a median of 6 days preoperatively.

**Inclusion criteria:** adults (age >18), any gender, scheduled to undergo elective surgery at the SFVAMC. Daily smokers based on self-report of at least 2 cigarettes/day and having smoked in the last 7 days. Presenting to APO clinic at least 3 days preoperatively.

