**Secondary outcomes:**

1. Descriptive outcomes of proportion of veterans eligible for inclusion, reasons for exclusion, and proportion of eligible veterans consenting to participate. Acceptability outcomes of satisfaction and use of intervention (any versus continuous) 8-weeks after randomization.

2. Smoking status at 8-weeks after randomization, as confirmed by exhaled CO.

3. Smoking reduction on the day of surgery and at 8-weeks after randomization (defined as 50% or less of baseline cigarettes smoked per day). Dual use of e-cigarettes and conventional cigarettes will also be assessed.

4. Bedside spirometry FEV1 (forced expiratory volume in first second), FVC (forced vital capacity), and cotinine level at 8-weeks after randomization (compared to baseline).

5. Postoperative complications or mortality within 30-days (by telephone self-report + chart review)

6. PACU length-of-stay

7. Hospital length-of-stay

8. Long-term assessment at 6 months - self-reported smoking status, including dual use of e-cigarettes.

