## Sample size estimation:

Previous perioperative studies have shown an absolute difference in smoking cessation rates between intervention and control groups to be 13-76%, with quit rates in the control groups ranging from 4-65%[^4-7^](#_ENREF_4). The proposed sample size is 30 (20 intervention, 10 control), balancing cost against precision, as is conventional for a pilot study. We realize that since the sample size is small, between-group differences may not be statistically significant. However, the proposed sample size will provide rough estimates of Aim 1 (smoking cessation) and Aim 4 (postoperative complications) treatment effects, residuals, and within-subject correlations needed for the full-scale trial. The sample size will also establish the acceptability of the intervention (Aim 2). In order to proceed with a full trial assigning ENDD use to a larger number of veterans, we would like to determine from this pilot study if ENDD is more acceptable to patients than NRT, as reported in previous qualitative studies[^11^](#_ENREF_11). The proposed sample size will have 80% power to detect an effect size of 1.085, accepting an alpha of 0.05 and assuming the standard deviation of a likert scale (0-7) of satisfaction with the intervention (ENDD or NRT) is around 1.0[^37^](#_ENREF_37). Even if we are underpowered to see smaller differences, the point estimates and confidence intervals will provide rough estimates that will be useful in planning a future study.

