## Randomization and blinding:

After collection of baseline data, randomization will be done by computer-generated scheme with randomly permuted block sizes of 3 or 6 in a 2:1 fashion. Allocation will be concealed by consecutively numbered, sealed, opaque envelopes. Due to the nature of the intervention, blinding of subjects is not possible. whenever possible, healthcare providers will be blinded throughout the perioperative period. However, patients may report being in the study to their providers, which may inadvertently cause unblinding. Outcome adjudicators will be blinded.

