## Statistical analysis plan:

Descriptive statistics to assess feasibility:

-proportion ineligible for inclusion (95% CI by bionmial exact) and reasons for exclusion

-proportion of eligible veterans declining to participate (95% CI by binomial exact)

Baseline characteristics to be collected prior to randomization: age, gender, race/ethnicity, comorbidities (hypertension, coronary artery disease, chronic obstructive pulmonary disease, diabetes mellitus, other cardiac disease), scheduled surgical procedure and subspecialty, smoking habits (number of cigarettes per day, years smoking), Fagerstrom score for nicotine dependence. Operative day information to be collected in addition to outcomes listed below: surgical procedure, duration of surgery, anesthesia type (local/monitored anesthesia care/regional/general/combined)

| **Outcome** | **Data Description** | **Likely Distribution** | **Hypothesis Test** |
| --- | --- | --- | --- |
| Smoking cessation (primary outcome) | Proportion | n/a | Fisher’s exact test |
| Smoking reduction | Proportion | n/a | Fisher’s exact test |
| Smoking amount | Cigarettes/day, Continuous  Median (IQR) | Normal or skewed (plot histogram) | Normal: two-sided t-test  Skewed:Wilcoxon rank-sum |
| Unanticipated hospital admission | Proportion | n/a | Fisher’s Exact Test |
| Hospital length of stay | Days  Continuous  Median (IQR) | Skewed | Time-to-event using Cox proportional hazards model; graph Kaplan-Meier plot |
| 8-weeks after randomization: Agreement to (0-7 likert) "I was satisfied with product I was given (e-cigarette or patch) to help me quit" (and similar questions regarding how helpful they found it, and whether they would recommend e-cig/patch) | Likert 0-7, Ordinal, Median (IQR) | Skewed | Wilcoxon rank-sum |
| 8-weeks after randomization: During the 6-weeks after you entered the study, how often did you use the product you were given (e-cigarettes or patch)?  Everyday, most days, a few times a week, once a week, less than once a week, did not use at all | Proportion that used everyday Proportion that did not use at all. | n/a | Fisher’s exact test |
| Change in FEV1, FVC, salivary cotinine | Liters, Continuous (Mean, SD) | Normal | Paired t-test |
| Composite of 30-day postoperative complications and mortality | Proportion | n/a | Fisher’s Exact Test |
| Duration in PACU | Hours  Continuous  Median (IQR) | Skewed | Time-to-event using Cox proportional hazards model; graph Kaplan-Meier plot |

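### The only test named for change in FEV1, FVC and salivary cotinine is a paired t-test, so these three secondary outcomes get no comparison of the randomised arms

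*Protocol*

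**What the plan says.** The design is a "Randomized controlled trial with 2 parallel arms", allocated by "randomly permuted block sizes of 3 or 6 in a 2:1 fashion". Under Sample size estimation: "The proposed sample size is 30 (20 intervention, 10 control".

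Aim 1 is comparative: "To determine how e-cigarettes plus counselling compare to transdermal nicotine replacement plus counselling for the achievement of smoking cessation". The text under that aim adds that "bedside spirometry readings will be assessed as secondary outcomes". Cotinine is not mentioned there. It appears in item 4 of the secondary outcomes, together with FEV1 and FVC, as "cotinine level at 8-weeks after randomization (compared to baseline".

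The outcome table in the Statistical analysis plan gives these three measures one shared row: "Change in FEV1, FVC, salivary cotinine | Liters, Continuous (Mean, SD) | Normal | Paired t-test". No other section names a test for them. The remaining rows of the table use Fisher's exact test, a two-sided t-test or Wilcoxon rank-sum test, or a Cox model, all of which can compare independent groups.

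**The concern.** The two arms contain different people, and no pairing across arms exists. The only pairing a paired t-test can use here is baseline with 8 weeks in the same participant. Its null hypothesis is that the mean within-person change is zero, and treatment arm does not enter.

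Followed literally, the row can be run in two ways, and neither compares e-cigarettes with patches.

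- Pooled over all 30 participants, it ignores allocation.
- Run within each arm, it gives two p-values from groups of 20 and 10. The reader is then tempted to compare one that is significant with one that is not.

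Elective surgery falls between the two measurements, so a within-person change mixes any effect of the product with surgery, recovery and time. Only the contrast between randomised arms separates these.

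At stake is whether a within-arm p-value for lung function or cotinine is later reported as a product effect. The pilot would also fail to deliver, for these measures, the treatment-effect estimates that the sample-size section says the full trial needs.

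**Working it through.** **Inputs from the Protocol.** 20 and 10 participants (Sample size estimation); 2:1 allocation (Randomization and blinding); alpha 0.05 (Sample size estimation). Two-sided testing is stated only in the smoking-amount row and is assumed here. The documents give no SD, correlation or expected change for FEV1, FVC or cotinine, so the true change d is expressed in SDs of the within-person change and varied.

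**The plan's own power figure.** The Protocol claims "80% power to detect an effect size of 1.085, accepting an alpha of 0.05" for the satisfaction score, with SD 1.0. Two-sample normal approximation:

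(1.960 + 0.842) × 1.0 × √(1/10 + 1/20) = 2.802 × 0.3873 = 1.085

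The figure reproduces. It is a between-arm calculation for a different outcome and does not depend on this point.

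**Paired test run within each arm.** Power of a two-sided paired t-test with n pairs comes from the non-central t distribution with n − 1 degrees of freedom and non-centrality d√n. Assume the same true d in both arms, so that the arms do not differ. Because the arms are independent,

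P(significant in one arm only) = P20(1 − P10) + P10(1 − P20)

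| Assumed common change d (SD) | P20 | P10 | Significant in one arm only |
| --- | --- | --- | --- |
| 0 | 0.050 | 0.050 | about 10% |
| 0.2 | 0.136 | 0.088 | 20% |
| 0.3 | 0.247 | 0.136 | 32% |
| 0.5 | 0.565 | 0.293 | 53% |
| 0.8 | 0.924 | 0.616 | 40% |
| 1.0 | 0.989 | 0.803 | 20% |
| 1.2 | 0.999 | 0.920 | 8% |

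At d = 0.5: 0.565 × 0.707 + 0.293 × 0.435 = 0.40 + 0.13 = 0.53. The 0.40 is the e-cigarette arm alone and the 0.13 the patch arm alone. The imbalance arises only because one arm is twice the size of the other. The change detectable with 80% power is 0.66 SD with 20 patients and 1.00 SD with 10.

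**Paired test pooled over 30.**

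- Both arms change by 0.5 SD: the paired test rejects in 75% of trials although the arms do not differ. A two-sample t-test on change rejects in 5%.
- The arms change by +0.36 and −0.72 SD, values built so that the pooled mean is (20 × 0.36 − 10 × 0.72)/30 = 0: the paired test rejects in 3% of 20,000 simulated trials and the two-sample test on change in 77%. A real arm difference can therefore vanish.

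**What a between-arm analysis could detect (80% power, normal approximation).** A two-sample test on change detects 1.085 SD of the change. ANCOVA detects 1.085 × √(1 − ρ²) SDs of the outcome, where ρ is the assumed correlation between baseline and 8 weeks:

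| ρ (assumed) | Detectable difference (outcome SD) |
| --- | --- |
| 0.5 | 0.94 |
| 0.7 | 0.77 |
| 0.8 | 0.65 |
| 0.9 | 0.47 |

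**The case against.** **The row matches the outcome as defined.** Item 4 of the secondary outcomes is a comparison with baseline, and a paired t-test is a valid test of that. This stands as far as description goes. It does not supply the arm comparison that a randomised trial exists to make and that Aim 1 asks for. A mean and SD of change reported by arm would let someone compute an arm difference, but the plan does not say to do so.

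**Aim 1 can still be answered.** A reader might infer from this row that the trial cannot answer Aim 1. The documents do not support that. The aim concerns smoking cessation, its primary outcome has Fisher's exact test, and so does smoking reduction. Only the spirometry part of Aim 1 is affected, and cotinine is not placed under that aim at all.

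**The 53% is conditional.** It lies near the peak of the range. It also requires separate within-arm tests whose significance is then compared, and the Protocol states neither step. Both points stand, so the whole range is shown. The absence of an arm term depends on no assumed effect size.

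**Cotinine.** Litres is plainly a clerical slip from sharing a cell with the spirometry measures. A reader might conclude that cotinine change must be skewed. That is plausible, since both regimens end with a nicotine-free week before the 8-week visit, so abstainers and continuing smokers should differ widely. But no figure in the documents shows it, and the column heading claims only a likely distribution.

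**It is a pilot.** The Protocol concedes that arm differences may not reach significance. That limits the severity. It does not excuse the choice of test, because the same section wants rough treatment-effect estimates with confidence intervals, and a paired test provides none for the arm difference.

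**Conclusion.** The point holds for the three change outcomes and no further. The row fixes one hypothesis test, that test never compares the randomised arms, and no other section adds one that does. This follows from the text alone.

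The size rests on assumptions: normal within-person changes, an equal true change in both arms, and two-sided alpha of 0.05. If the test is run by arm, the chance of significance in one arm only ranges from about 8% to 53% over common changes of 0 to 1.2 SD. If it is pooled, a shared change of 0.5 SD gives a significant result in 75% of trials with no arm difference behind it.

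Severity is moderate. These are secondary outcomes of a 30-patient pilot. The analyses of cessation, smoking reduction, acceptability and complications are untouched, and the comparison can be added before the data are analysed.

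**What to change.** In the outcome table of the Statistical analysis plan:

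1. For FEV1 and FVC, replace the paired t-test with ANCOVA of the 8-week value on arm and baseline value, reporting the adjusted arm difference with its 95% CI. A two-sample t-test on change would also restore the randomised comparison. ANCOVA is preferred because it detects smaller differences at every correlation examined.
2. Keep within-arm change (mean, SD) as description, without using within-arm p-values to compare products.
3. Give cotinine its own row with its own concentration unit and the same ANCOVA. State beforehand that a log-scale or rank-based baseline-adjusted analysis will be used if its distribution is skewed.

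The cost is one table row reworded and one added. No new data are needed, since baseline and 8-week values are already planned, and the sample size does not change.

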## Qualitative Analysis:

Individual interviews will be performed 8-weeks after randomization to determine patient attitudes towards e-cigarettes and nicotine patches perioperatively. Specifically, we will solicit information from patients regarding their perceptions of how the intervention (e-cigarette or nicotine patch) affected their willingness and/or success at quitting. Thematic and content analysis will be used to identify core concepts and to develop categories for coding interview data. Content analysis will be used to systematically sort and code information based on themes.

## Timetable:

In 2013, the SFVAMC had 3914 cases, averaging 325 cases per month. Roughly 70% of the cases are elective, or around 230 per month. Around 20% are smokers, so each month, we expect to encounter 45 smokers. Since only half are expected to present to preadmission at least 1-week prior to surgery and we anticipate a recruitment rate of 50% of smokers, or around 10 per month. Therefore, we expect pilot study recruitment to take 3 months. The primary end-point data is anticipated to be collected by around 1 month after recruitment finishes, with secondary end-points collected after another month.

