# 16. Budget

**Awarded funding: $18,569 from internal UCSF Department of Anesthesia funds**

**Amount from UCSF RAP: $29,969**

**Total research budget: $48,538**

**Personnel-**Research Assistants

One full-time research assistant (healthcare professional with previous experience in patient interaction) at 40 hours per week and one part-time research assistant at 17.5 hours per week, each at a rate of $25.29/hr will be hired. Two research assistants are needed in order to ensure that the research assistant performing the randomization is different than the one collecting post-randomization data (i.e. to maintain blinding). We anticipate that during the first and last months of the study, we will require fewer hours since few patients will be booked for surgery within the first few weeks and no new patients will be recruited in the final 1-2 months of the study, while outcome data will continue to be collected.

Therefore, the two assistants will overlap by 4.5 months, so there will be 6 months of total coverage.

|  | Hours per week | Hourly rate | Benefits | Weekly rate | Number of weeks | Total cost |
| --- | --- | --- | --- | --- | --- | --- |
| Full-time | 40 | 25.29 | 41.72% | 1433.64 | **20** | $30,106.43 |
|  |  |  |  |  |  | $30,106.43 |

Fringe benefits are calculated using the UCSF established rates of 41.72% for 'Staff Personnel – career'.

Apart from the research assistants, no other salary support is being requested. I ([name]) have 70% protected research time, as part of the Clinical Instructorship with Research Training, that I will devote in part to this trial.

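### Secondary outcome 8, at 6 months, falls due in about study months 6 to 9, but the timetable has secondary data in by about month 5 and assistant cover totals 6 months, so it is neither scheduled nor staffed

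*Protocol*

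**What the plan says.** Three parts of the protocol bear on this.

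- **Outcomes, secondary outcome 8:** "Long-term assessment at 6 months - self-reported smoking status, including dual use of e-cigarettes". The section does not say whether the 6 months run from randomization or from surgery.
- **Timetable:** recruitment is expected to take 3 months. After that, "The primary end-point data is anticipated to be collected by around 1 month after recruitment finishes, with secondary end-points collected after another month". No exception is made for outcome 8.
- **Budget, Personnel:** "the two assistants will overlap by 4.5 months, so there will be 6 months of total coverage". The same paragraph expects recruitment to be closed only for the last 1 to 2 months of the study, while outcome data are still coming in.

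No section schedules a contact about 6 months after the last enrolment or says who would make it.

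**The concern.** The three statements do not fit together. With 3 months of recruitment, follow-up that ends 2 months after the last enrolment cannot contain a 6-month assessment of that participant, and 6 months of assistant cover reaches almost nobody's 6-month date.

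Outcome 8 is the only outcome later than 8 weeks. Study product is supplied for 6 weeks, so it is also the only planned look at smoking well after supply ends. Aim 2 includes testing the feasibility of follow-up procedures for a larger trial. If the 6-month contacts are left to improvisation, the pilot says little about whether follow-up of that length works.

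Study length, follow-up times and staffing are stated in this protocol, so the mismatch is between its own figures. It is not a detail left to an analysis plan.

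**Working it through.** **Inputs.** From Timetable: 3914 cases in the year 2013, an elective share of 70%, a smoker share of 20%, half of the smokers seen early enough, and half of those recruited, which the protocol puts at about 10 per month. From Sample size estimation: 30 participants (20 and 10). From Budget: 6 months of cover. From Detailed Experimental Design and Methods: a median of 6 days between the preoperative clinic visit and surgery. My assumptions are even accrual from month 0, a month of 30.44 days, and cover that starts with enrolment.

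**1. The plan's recruitment figure.** 3914 / 12 = 326.2 cases per month. Then 326.2 × 0.70 = 228.3 elective, × 0.20 = 45.7 smokers, × 0.50 = 22.8 early enough, × 0.50 = 11.4 recruited. The protocol rounds this to about 10. 30 / 10 = 3.0 months, which reproduces the stated duration. Unrounded, 30 / 11.4 = 2.6 months.

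**2. End of secondary data collection in the timetable.** 3 + 1 + 1 = month 5.

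**3. Outcomes that fit.** The last 8-week visit is at 3 + 56 / 30.44 = 3 + 1.84 = month 4.8. The last 30-day assessment, with surgery at the median 6 days (0.20 month), is at 3 + 0.20 + 30 / 30.44 = about month 4.2. Both fall before month 5.

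**4. When outcome 8 falls due.** Entry times run from 0 to 3, so 6-month dates run from 0 + 6 = month 6 to 3 + 6 = month 9. Counted from surgery at the median 6 days, they run from about 6.2 to 9.1 or 9.2.

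**5. How many have reached 6 months by each date** (entry of patient i at the middle of its 0.1-month slot, counted from randomization):

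| Study month | Reached 6 months, of 30 |
| --- | --- |
| 5 (timetable end) | 0 |
| 6 (end of cover) | 0, or 1 if the first patient is randomized on day 0 |
| 7 | 10 |
| 8 | 20 |
| 9 | 30 |

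**6. Sensitivity.** With recruitment in 2.6 months, due dates run from about 6.0 to 8.6, and the count is still 0 of 30 at the timetable end (month 4.6) and at month 6. The Budget does not say when cover begins relative to first enrolment. An earlier start widens the gap and a later one narrows it. For 6 months of cover to reach month 9 it would have to begin at 9 − 6 = month 3, when recruitment is over. That cannot be the intention, since the Budget has a research assistant performing the randomization.

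**7. Size of the gap.** 9 − 5 = about 4 months beyond the timetable, and 9 − 6 = about 3 months beyond assistant cover.

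**The case against.** A reader might infer that the 6-month outcome cannot be collected at all. The documents do not support that. The Timetable is a forecast in approximate terms and does not declare the study closed at month 5. That date matches the last 8-week visit (month 4.8), so the sentence was plausibly written around the 8-week outcomes and simply leaves item 8 out. Item 8 is self-report, with no breath test or spirometry attached. The Budget says that the investigator has 70% protected research time, part of it for this trial, so the end of paid assistant cover is not the end of all capacity. This objection stands against impossibility. It does not remove the mismatch, because no section gives anyone the task or a date.

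A reader might also infer that the study would fail to deliver a promised answer on long-term dual use. Background and Significance speaks only of how common dual use is in a controlled setting. Secondary outcome 3 includes dual use, and the 8-week interview asks about use of both products on the same day. That contribution survives without item 8.

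Nor can bias from incomplete 6-month contact be sized: the documents give no contact or loss rate.

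Finally, little else rests on item 8. It is the last of eight secondary outcomes in a 30-person pilot, it is absent from the abstract and the aims, and the analysis table has no row that names 6 months. This limits the importance of the point, but a listed outcome still needs a place in the schedule.

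**Conclusion.** The point holds as an inconsistency between Outcomes, Timetable and Budget. If the plan is followed as written, 0 of 30 six-month assessments fall due by the timetable's end of secondary data collection, and at most about 1 of 30 by the end of assistant cover. The first result needs only the stated 3-month recruitment and month-5 end, and it survives faster accrual. The second also assumes that cover starts with enrolment. The outcome is unscheduled and unstaffed, not uncollectable. The primary, 8-week and 30-day outcomes fit the timetable and are untouched. The correction is worth making before enrolment but does not threaten the trial's main results.

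**What to change.** Reconcile the three sections:

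- **Timetable:** state that recruitment runs in months 0 to 3, that day-of-surgery, 8-week and 30-day data are complete at about month 5, and that 6-month contacts run in about months 6 to 9.
- **Outcomes, item 8:** state that the 6 months are counted from randomization, as the 8-week outcomes already are.
- **Budget, Personnel:** assign the roughly 30 short contacts to existing staff, for example within the investigator's protected research time. The Budget separates the person who randomizes from the person who collects later data, and the principal investigator or a co-investigator observes the first 3 randomizations. The caller should therefore be someone not involved in allocation where possible.

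The cost is some wording, about 30 brief contacts, and a final dataset that closes about 4 months later (month 9 instead of month 5). Reporting of the primary and 8-week results need not wait for it.
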